### Interventions

Eligible patients will be randomized in equal proportions in 2 groups. In 50% of patients, the preoperative study of anatomical structures will be performed with the standard method of chest CT evaluation using classic two-dimensional reconstructions (axial, coronary, and sagittal). In the remaining 50% of patients, in addition to the 2D reconstruction, a 3D reconstruction (volume rendering) of the vessels and bronchi of the chest CT will be performed using special software to have a more profound knowledge of the anatomical structures.

3D reconstructions can be performed through the use of Horos (Osirix), a free, open-source medical imaging software program. If necessary, trial participants can change the software. The 3D reconstruction is semi-automatic. After a short learning curve, if preferred, it will take around 45 min.

### Outcomes (see supplementary file for outcome definition)

Primary outcomes measuresDisease-free resection margin. This measure of success was selected because it was considered clinically and oncologically relevant after segmentectomy and represented a prerequisite and necessary quality control. A disease-free resection margin > 2 cm is mandatory, and a significant result could improve clinical practice and therapeutic outcomes.Evaluation of conversions from minimally invasive to thoracotomy procedure. It is still unclear whether preoperative 3D anatomical reconstruction can reduce the incidence of major intraoperative events, which usually require a traditional thoracotomy. This measure of success, if significant, will increase patient safety.

Secondary outcomes measuresEvaluation of operating timesEvaluation of intraoperative blood lossEvaluation of vascular lesionsEvaluation of intraoperative air leaks and the use of sealantsEvaluation of postoperative air leaksEvaluation of postoperative hospitalization length

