### Eligibility criteria

Patients (or a representative) must provide written, informed consent before any study procedures occur.

Inclusion criteria

Patients eligible for the trial must comply with all the following at randomization:Segmentectomy performed through a MI approach (VATS or RATS)Pathologically proven NSCLC on the resected specimenAge ≥ 18

Exclusion criteriaPrior homolateral cardiothoracic surgeryAllergy or any other contraindication to iodinated contrast mediaSegmentectomy performed through an open approach (thoracotomy)Histology different than NSCLCPregnancy

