### Participant timeline

Patients with tumors < 2 cm in diameter and suspicion of malignancy will undergo CT and be discussed at the Multidisciplinary Board of Thoracic Oncology. Patients selected for MI segmentectomy will conduct an informational interview and possibly sign the consent to the study. Patients who agreed to participate will be randomized into two groups:Group 1: 2D + 3D reconstructionGroup 2: 2D reconstruction (control group)

Subsequently, a database will prospectively collect intraoperative and postoperative data. The follow-up will be closed one month after surgery (Fig. 3).

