### Sample size

No data in the current literature was found about the other primary outcome margin- and disease-free resection. Therefore, the sample size was calculated based on the primary outcome conversions from minimally invasive to thoracotomy procedure.

To calculate sample size, we use data about conversion derived from previous literature [17–21]. The conversion rate for patients in the 2D group is estimated to be 9.4% [19]; the retrospective study has shown a reduction to 2.6%. Therefore, the required sample size to confirm superiority was 274, with a power of 80%, a one-sided significance level of 0.05, an accrual period of 3 years, and a follow-up period of 1 month. The planned total sample size was set at 288 patients to account for loss at follow-up.

Systematic methods such as reminders to contact patients, make appointments, and monitor retention will be employed to improve participant retention and will not expenses for follow-up visits and procedures.

We have used for the sample size determination the R software (package pwr) [26].

Two pre-specified interim analyses were conducted after the accrual of half of the planned patients and after accrual completion. To keep the study at a 5% one-sided significance level, we used the Lan–DeMets alpha-spending function [27] with an O’Brien–Fleming approach [28].

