### Blinding (masking)

The trial participants will remain blinded to the group to which they belong to avoid any decision to withdraw from the trial. Even the pathologist does not know the assignment. The measures of outcomes are objective measures; this avoids ascertainment bias. However, outcome assessors and data analysts are kept blinded to the assignment. It is not possible to mask the assignment to the surgeons. This could induce a performance bias; it will be discussed in the limitations of the study.

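### Eligibility depends on the surgical approach actually performed, which unmasked surgeons settle after randomisation, so a patient opened upfront can drop out of the conversion comparison

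*Protocol article*

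**What the plan says.** All sections cited are in the protocol article.

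- **Outcome.** Outcomes lists "Evaluation of conversions from minimally invasive to thoracotomy procedure" as a primary outcome. The stated reason is that it is unclear whether 3D reconstruction "can reduce the incidence of major intraoperative events, which usually require a traditional thoracotomy". The section heading refers the reader to a supplementary file for definitions.
- **Sizing.** Under Sample size, "the sample size was calculated based on the primary outcome conversions from minimally invasive to thoracotomy procedure".
- **Eligibility.** The inclusion list opens with "Patients eligible for the trial must comply with all the following at randomization", and its first item is "Segmentectomy performed through a MI approach (VATS or RATS". The exclusion list contains the mirror image, a segmentectomy carried out by thoracotomy. Another inclusion item is NSCLC confirmed on the specimen removed, also a fact available only after the operation.
- **Order of events.** Participant timeline says "Patients selected for MI segmentectomy will conduct an informational interview and possibly sign the consent to the study", and then "Patients who agreed to participate will be randomized into two groups". Surgery follows.
- **Masking.** Under Blinding, "It is not possible to mask the assignment to the surgeons". Under Interventions, only one arm receives the 3D reconstruction.
- **Analysis set.** Data collection seeks to limit the number of patients who become ineligible once randomised. It also says that participants stay in their allocated group, and that those with a missing primary outcome are excluded.

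**The concern.** The surgical approach used is decided after randomisation by someone who knows the arm, and the intervention is a planning aid that could influence that decision. A 3D-arm surgeon who foresees difficult anatomy might open from the start. Followed as worded, the eligibility criteria then make that patient ineligible. A similar 2D-arm patient might start minimally invasively and be counted if converted.

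Selection on a post-randomisation fact that treatment can affect breaks the comparability that randomisation provides. The outcome exposed to this is the one that sizes the trial and supports its patient-safety claim. The promise to analyse patients as randomised would protect against this, but the eligibility wording and the expectation of late ineligibility point the other way, and the article does not say which prevails.

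**Working it through.** **1. The plan's own figure.** Inputs from Sample size: 9.4% conversion with 2D, 2.6% with 3D, one-sided 0.05, power 80%, R package pwr. The arcsine effect size is h = 2·asin(√0.094) − 2·asin(√0.026) = 0.2993. Then n = 2·[(z₀.₉₅ + z₀.₈₀)/h]² = 138.01 per arm, or 276 to 278 in total, against 274 stated. That is close enough; the sample size arithmetic is not the issue here. The planned total of 288 gives 144 per arm.

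**2. When each fact is known.**

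| Step | What is known | Section |
|---|---|---|
| Selected for minimally invasive segmentectomy, consent | Planned approach | Participant timeline |
| Randomisation | Inclusion criteria said to be met | Eligibility criteria |
| Planning, with or without 3D | Arm known to the surgeon | Interventions; Blinding |
| Operation | Approach performed | Eligibility criteria |

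The criterion is worded for the last row but is meant to be checked at the second.

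**3. Illustration of size.** Assumptions: the true need for thoracotomy is T = 9.4% in both arms, and there are 144 patients per arm. A share f of 3D-arm thoracotomies is done upfront and dropped, and none in the 2D arm. The documents give no value for f or for any difference between arms.

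- Expected thoracotomies per arm: 144 × 0.094 = 13.5.
- Expected 3D-arm patients dropped: 13.5 × f.
- Analysed 3D conversion rate: T(1 − f)/(1 − T·f). For f = 25%: 0.0705/0.9765 = 7.2%.
- Chance of declaring 3D superior: exact enumeration of Fisher's test, with the number dropped binomial (144, T·f).

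| f | Dropped | 2D rate | 3D rate | One-sided 0.05 | Two-sided 0.05, favouring 3D |
|---|---|---|---|---|---|
| 0% | 0 | 9.4% | 9.4% | 3.3% | 1.6% |
| 10% | 1.4 | 9.4% | 8.5% | 5.6% | 3.0% |
| 25% | 3.4 | 9.4% | 7.2% | 11.7% | 7.3% |
| 50% | 6.8 | 9.4% | 4.9% | 33.8% | 25.9% |

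Both columns are shown because Sample size uses a one-sided level and Statistical methods a two-sided one.

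**4. If the patient is kept instead.** Counted as having no conversion, the upfront-open patient stays in the denominator and the 3D rate is T(1 − f): 8.5%, 7.1% and 4.7%. The one-sided chances are 5.8%, 12.6% and 37.3%. Keeping the patient therefore restores the randomised comparison but does not by itself show whether thoracotomies fell or only moved to the start of the operation. Counting any thoracotomy in all randomised operated patients gives 9.4% in both arms and returns the chance to 3.3%.

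**The case against.** **The event definition is not shown.** The supplementary file may say how an upfront thoracotomy is handled. This stands, so one cannot assert that such a case is never an event. It does not resolve the conflict between eligibility and as-randomised analysis in the article itself.

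**The criterion may mean intended approach.** Inclusion criteria are said to apply at randomisation, and only patients already selected for minimally invasive surgery are randomised. That is a reasonable reading and probably the intended one, but it is not what the words say. The specimen-based histology item and the expectation of late ineligibility both support the literal reading.

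**The exclusion applies to both arms.** Correct. A reader might infer that the rule removes thoracotomies selectively from the 3D arm. The documents do not support that: selectivity comes only from assumed surgeon behaviour.

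**Avoiding a mid-operation conversion may be a real benefit.** This also stands. Primary objective and Outcomes target major intraoperative events, and a thoracotomy chosen beforehand is arguably not one. It is the reason to keep conversion as primary rather than replace it with any thoracotomy, on which the trial is not sized.

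**The shares have no anchor.** Correct. A share near 75% would bring the 3D rate to about the planned 2.6%, but such a share would be picked to match, so the agreement is no evidence that the expected effect is an artefact.

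**Conclusion.** The point holds as an unresolved conflict that leaves the sized comparison open to post-randomisation selection. Eligibility rests on the approach performed, an unmasked surgeon decides that after allocation, and Data collection points both ways on whether such patients stay in.

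Whether bias follows depends on two things the documents do not give: that the criterion is applied as worded, and that upfront opening differs by arm. Under the stated assumptions, false superiority on the one-sided Fisher test rises from 3.3% to about 6%, 12% and 34% at shares of 10%, 25% and 50%. Small shifts do little; serious inflation needs a large one. The direction towards 3D is plausible but assumed.

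A reader might also infer that every converted patient is excluded, since the operation ended open, leaving no events at all. The documents do not support this: Outcomes makes conversion a primary outcome, Sample size is built on it, and Harms says it will be collected.

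**What to change.** - **Eligibility criteria:** define the approach criterion, in both the inclusion and exclusion lists, as the approach planned before randomisation.
- **Eligibility criteria and Data collection:** state that patients opened upfront and patients converted remain in the as-randomised analysis, and that an upfront-open patient's conversion outcome is not treated as missing.
- **Outcomes and Statistical methods:** keep conversion as the primary outcome. Pre-specify a sensitivity analysis of any thoracotomy at the index operation, upfront or converted, in all randomised operated patients, and report upfront thoracotomies by arm.

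The first two changes are wording only. The third adds one analysis, using the approach already in the operative record. Its downside is small: the trial is not sized for it, and the any-thoracotomy rate may lie somewhat above the 9.4% planning figure, which covers conversion alone.

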### Participant timeline

Patients with tumors < 2 cm in diameter and suspicion of malignancy will undergo CT and be discussed at the Multidisciplinary Board of Thoracic Oncology. Patients selected for MI segmentectomy will conduct an informational interview and possibly sign the consent to the study. Patients who agreed to participate will be randomized into two groups:Group 1: 2D + 3D reconstructionGroup 2: 2D reconstruction (control group)

Subsequently, a database will prospectively collect intraoperative and postoperative data. The follow-up will be closed one month after surgery (Fig. 3).

**Fig. 3 Fig3:**
[figure not shown]
Flow of participants

### Sample size

No data in the current literature was found about the other primary outcome margin- and disease-free resection. Therefore, the sample size was calculated based on the primary outcome conversions from minimally invasive to thoracotomy procedure.

To calculate sample size, we use data about conversion derived from previous literature [17–21]. The conversion rate for patients in the 2D group is estimated to be 9.4% [19]; the retrospective study has shown a reduction to 2.6%. Therefore, the required sample size to confirm superiority was 274, with a power of 80%, a one-sided significance level of 0.05, an accrual period of 3 years, and a follow-up period of 1 month. The planned total sample size was set at 288 patients to account for loss at follow-up.

Systematic methods such as reminders to contact patients, make appointments, and monitor retention will be employed to improve participant retention and will not expenses for follow-up visits and procedures.

We have used for the sample size determination the R software (package pwr) [26].

Two pre-specified interim analyses were conducted after the accrual of half of the planned patients and after accrual completion. To keep the study at a 5% one-sided significance level, we used the Lan–DeMets alpha-spending function [27] with an O’Brien–Fleming approach [28].

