### Statistical methods

We do not expect a relevant degree of missing data. Methods of multiple imputations (bagged trees imputation) will be used to calculate missing values.

Multivariable analyses will be based on logistic regression for binary outcomes and linear regression for continuous outcomes.

We will examine the residual to assess model assumptions and goodness-of-fit. *P*-values will be reported to three decimal places, with *p*-values less than 0.001 reported as *p* < 0.001. All analyses were performed using the R Statistical Software (4.2.2; R Core Team 2022). We will use 2-sided *p*-values with alpha ≤ 0.05 significance level for all tests.

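### Conversion is sized at one-sided 0.05 but all tests are set at two-sided 0.05; the two rules conflict, and the planned Fisher test does not reach the stated 80% power under either

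*Protocol article*

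**What the plan says.** All references are to the protocol article.

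- **Sample size, sizing sentence.** Conversion is the outcome used for sizing, with 9.4% assumed in the 2D group and 2.6% with 3D reconstruction. The calculation was made "with a power of 80%, a one-sided significance level of 0.05", and "the required sample size to confirm superiority was 274". Then: "The planned total sample size was set at 288 patients to account for loss at follow-up". The software named is the R package pwr.
- **Sample size, interim paragraph.** The one-sided level is repeated as the overall error rate for the alpha-spending plan: "To keep the study at a 5% one-sided significance level".
- **Statistical methods.** "We will use 2-sided" p-"values with alpha ≤ 0.05 significance level for all tests".
- **Abstract, Methods and analysis.** Fisher's exact test is named for binary outcomes, and conversion is listed among the primary endpoints.
- **Trial design.** Allocation is 1:1.

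No section exempts conversion from the two-sided rule or explains how the two levels fit together.

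**The concern.** A two-sided test at 0.05 allows an error of 0.025 in the direction of benefit. Sample size allows 0.05 in that direction. Both statements cover the conversion comparison, so the plan has two success criteria for the one primary outcome on which it was sized.

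Two things are at stake. First, some results would be a success under one section and a failure under the other. If this stays open until the data are seen, the criterion can be chosen with knowledge of the result. Second, the 80% power was computed under the one-sided rule, so it does not describe a trial analysed under the two-sided rule.

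A related but separate matter affects the same figure: the sizing formula is an approximation that is more optimistic than the exact test planned for the analysis.

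**Working it through.** **Inputs.** Conversion 9.4% against 2.6%, 80% power, one-sided 0.05, totals 274 and 288, R package pwr (all Sample size); 1:1 allocation (Trial design), so 137 or 144 per arm; two-sided 0.05 for all tests (Statistical methods); Fisher's exact test (Abstract).

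**Step 1: reproduce the plan's figure.** The pwr package uses the arcsine effect size:

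h = 2·asin(√0.094) − 2·asin(√0.026) = 0.6232 − 0.3239 = 0.2993

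n per arm = 2·((z_α + z_power)/h)² = 2·((1.645 + 0.842)/0.2993)² = 138.0

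That is 276 to 278 in total, against 274 stated, a gap below 3%. The usual alternatives at one-sided 0.05 are further off: 300 (pooled), 296 (unpooled) and 356 (continuity-corrected). The stated 274 is therefore in effect the one-sided arcsine result.

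**Step 2: same formula under each rule.** Power = Φ(h·√(n/2) − z_α). At 137 per arm h·√(n/2) = 2.477; at 144 per arm it is 2.540.

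| Arcsine formula | 274 | 288 |
|---|---|---|
| One-sided 0.05 (z = 1.645) | Φ(0.832) = 79.7% | Φ(0.895) = 81.5% |
| Two-sided 0.05 (z = 1.960) | Φ(0.517) = 69.8% | Φ(0.580) = 71.9% |

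Sidedness alone therefore costs about 10 points: 79.7 − 69.8 = 9.9 at 274.

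**Step 3: the test named in the Abstract.** Fisher's exact power is the sum of the binomial probabilities of all pairs of conversion counts whose p-value is at or below 0.05, at the assumed rates.

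| Fisher's exact test | 274 | 288 |
|---|---|---|
| One-sided 0.05 | 70.1% | 72.6% |
| Two-sided 0.05 | 57.7% | 60.7% |

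At two-sided 0.05, moving from the arcsine formula to Fisher's test costs a further 69.8 − 57.7 = 12.1 points at 274 and 71.9 − 60.7 = 11.2 points at 288.

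**Step 4: results on which the two rules disagree.** Examples with 137 per arm (2D against 3D conversions), Fisher's test:

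| Conversions | One-sided p | Two-sided p |
|---|---|---|
| 11 v 3 | 0.026 | 0.051 |
| 12 v 4 | 0.034 | 0.068 |
| 14 v 5 | 0.027 | 0.055 |

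Each succeeds under Sample size and fails under Statistical methods. At the plan's assumed rates, the chance of such a result is 70.1 − 57.7 = 12.4% at 274 and 72.6 − 60.7 = 11.9% at 288.

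**For scale only.** At two-sided 0.05, 80% power would need 2 × 176 = 352 patients by the arcsine formula and about 410 with Fisher's test, before any allowance for loss.

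**The case against.** Five objections deserve an answer.

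- **The one-sided level may be what was meant.** Sample size states it twice, and the research hypothesis is directional. The two-sided rule is one general sentence. The documents do not show which statement is the slip, so the fall to about 70% on the plan's formula is conditional on the two-sided rule governing. This stands. The contradiction stands too, because that sentence covers all tests without exception.
- **Sidedness does not explain everything.** A reader might infer that the one-sided against two-sided mismatch by itself brings power down to 58–61%. It does not. It accounts for about 10 points on the plan's formula; the rest comes from sizing with an approximation and planning an exact test.
- **The one-sided rule does not rescue the figure.** A reader might also infer that 80% is right if the one-sided rule is kept. That is true only for the arcsine approximation. Fisher's test reaches 70–73% there.
- **Fisher's test is named only in the Abstract.** Statistical methods mentions logistic regression for multivariable analyses and does not repeat Fisher. Taking Fisher as the primary comparison of conversion is the natural reading, but the Step 3 figures depend on it.
- **The 288 figures are an upper bound.** The extra 14 patients are an allowance for loss, and Data collection excludes patients with missing primary outcomes. If the allowance is used up, the 274 figures apply.

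**Conclusion.** The inconsistency is real and needs correcting before analysis. Sample size sets one-sided 0.05 for sizing and for overall error, Statistical methods sets two-sided 0.05 for all tests, and the two rules disagree on about 12% of outcomes at the plan's own assumed rates.

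The sizing arithmetic itself is sound within rounding. What fails is the stated 80%:

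- If the two-sided rule governs, power by the plan's formula is 69.8% (274) to 71.9% (288).
- With Fisher's exact test it is 57.7% to 60.7% at two-sided 0.05 and 70.1% to 72.6% at one-sided 0.05, so 80% is not reached under either rule.

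These figures assume the plan's conversion rates, equal arms and, for the second item, Fisher as the test of conversion. The cost of alpha spending is not included; it is expected to be small and would lower the figures slightly.

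**What to change.** State one error rate in both Sample size and Statistical methods before any analysis, and restate the power at 274 and 288 under that choice.

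- **If two-sided 0.05 is kept** (the conventional choice): remove the one-sided wording from Sample size, in both the sizing sentence and the alpha-spending sentence. State power as about 58–61% with Fisher's exact test, or 70–72% by the approximate formula.
- **If one-sided 0.05 is kept for conversion:** exempt that test explicitly in Statistical methods, report a matching 90% confidence interval, and state power as about 70–73% with Fisher's exact test. An exemption alone is not enough, because it would leave the 80% claim in place.

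The choice is the sponsor's. The cost is wording in two sections and a less favourable stated power; no patients are added.

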**Methods and analysis:**

This is a prospective, randomized, controlled study.

Patients will be randomized into two groups:

1. Group 2D: the preoperative workup for these patients will consist of a contrast-enhanced chest CT with two-dimensional (2D) reconstructions (axial, coronary, and sagittal);

2. Group 3D: the preoperative workup for these patients will consist of a contrast-enhanced chest CT with two-dimensional (2D) reconstructions (axial, coronary, and sagittal) and a 3D reconstruction (volume rendering) of the same chest CT employing dedicated software.

The primary endpoints will be negative margin (R0) resection rate, resection margin (staple line-to-tumor distance), and thoracotomy conversions.

We will use Fisher’s exact test for binary outcomes and Mann–Whitney *U* test for continuous outcomes. For subgroup analyses, we will use regression. Multivariable analyses will be based on logistic regression for binary outcomes and linear regression for continuous outcomes.

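### The 80% power at 274 patients comes from a large-sample formula; the planned Fisher's exact test has about 70% at the same one-sided 0.05

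*Protocol article*

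**What the plan says.** The Sample size section bases the calculation on conversion from a minimally invasive procedure to thoracotomy. It takes 9.4% in the 2D group and 2.6% with 3D reconstruction, 80% power and "a one-sided significance level of 0.05". It concludes that "the required sample size to confirm superiority was 274", and then: "The planned total sample size was set at 288 patients to account for loss at follow-up". The tool is named: "We have used for the sample size determination the R software (package pwr").

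The test is named in the abstract, under Methods and analysis, which assigns Fisher's "exact test for binary outcomes". Conversion is a binary primary outcome. The Statistical methods section adds logistic regression for multivariable analyses and asks for two-sided p-values at 0.05. It names no other unadjusted test for conversion. Nowhere does the article say that the sample size allows for an exact test.

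**The concern.** The two-proportion function in pwr works with Cohen's h, the difference of arcsine-transformed proportions, and treats the test statistic as normal. Fisher's test conditions on the total number of events. With few events its attainable p-values are widely spaced, so its actual type I error lies well below the nominal level and power falls with it. A sample size from the first method does not deliver its nominal power under the second.

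The whole sample size rests on this one endpoint. If the power is overstated, the chance of missing the assumed effect is larger than the investigators, the ethics committees and the data monitoring committee have been told. This is separate from the conflict between the one-sided level in Sample size and the two-sided level in Statistical methods: the loss is already there at the plan's own one-sided 0.05.

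**Working it through.** **Inputs.** From Sample size: p1 = 0.094, p2 = 0.026, one-sided α = 0.05, power 0.80, N = 274 (137 per arm) and N = 288 (144 per arm). From Trial design: 1:1 allocation. From the abstract: Fisher's exact test. From Statistical methods, for the second set of results: two-sided α = 0.05.

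**Step 1: reproduce 274.**

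- h = 2·asin(√0.094) − 2·asin(√0.026) = 0.6232 − 0.3239 = 0.2993
- n per arm = 2·[(1.645 + 0.842)/h]² = 138.0, or 276 to 278 in total depending on rounding
- with h rounded to 0.30, n per arm = 137.4, or about 274 to 275 in total

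Other formulas for the same inputs do not come close:

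| Formula | Total N |
|---|---|
| One-sided, pooled variance | 300 |
| One-sided, unpooled variance | 296 |
| One-sided, continuity-corrected | 356 |
| Two-sided, arcsine | 352 |

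So 274 is the one-sided arcsine figure up to rounding. By that formula the power at 137 per arm is 79.7%.

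**Step 2: expected events.** 137 × (0.094 + 0.026) = 16.4 conversions at 274, and 144 × 0.120 = 17.3 at 288.

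**Step 3: exact power of Fisher's test.** Take X1 ~ Bin(n, 0.094) and X2 ~ Bin(n, 0.026). For each possible table compute Fisher's p-value from the hypergeometric distribution given X1 + X2, and sum the probabilities of the tables with p ≤ α.

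| | 137 per arm (274) | 144 per arm (288) |
|---|---|---|
| Arcsine approximation, one-sided 0.05 | 79.7% | 81.5% |
| Fisher, one-sided 0.05 | 70.1% | 72.6% |
| Fisher, two-sided 0.05 | 57.7% | 60.7% |

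**Step 4: where the power goes.** With a common conversion rate of 6% in both arms, the actual size of the one-sided 0.05 Fisher test is 2.7% at 137 per arm and 2.8% at 144. Over 40% of the nominal 5% is unused.

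**Step 5: what Fisher's test would need.** The smallest n giving 80% power is 169 per arm (338 evaluable patients) one-sided, or 205 per arm (410) two-sided, before any allowance for loss.

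**Step 6: other tests at 288, no losses.**

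| Test | One-sided 0.05 | Two-sided 0.05 |
|---|---|---|
| Fisher | 72.6% | 60.7% |
| Boschloo | 78.2% | 66.7% |
| Mid-p | 79.5% | 68.8% |
| Center-stratified CMH, no continuity correction | 81.3% | 70.7% |

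The CMH row is a simulation that assumes ten centers of equal size with the same conversion rates; the article gives no center-level figures. Its simulated one-sided size is about 4.9% to 5.4%. The mid-p test has one-sided size 4.5% at a 6% rate. At 274 one-sided, mid-p has 77.5% and CMH 79.4%.

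**The case against.** Fisher's test is valid. Its conservatism buys guaranteed control of type I error in sparse data, and the uncorrected CMH test can run slightly above its nominal level. That stands as a reason why someone might choose to keep Fisher's test. It does not make the stated 80% true for it.

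The planned enrolment is 288, so the fairer shortfall might be 73% against 80%. But the plan claims 80% at 274 and reserves the other 14 patients for loss, so 70% is the matching figure. Even with no loss the power stays below 80%.

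The fall to about 60% is largely due to the one-sided/two-sided conflict. That is right, and the conclusion here does not rely on it: about 10 points are lost at one-sided 0.05 alone.

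The word arcsine does not appear in the article, and 274 needs some rounding to reproduce. The named package and the number both point to it, but the conclusion does not depend on it. Fisher's power at 274 is the same whatever formula was used.

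The test is named only in the abstract of a condensed article. Nothing elsewhere contradicts it, and both the test and the power are stated, so this is not a detail left to an unseen analysis plan.

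The two unstratified alternatives also fall just short of 80% at 288. True, and whichever test is chosen needs its own power stated.

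**Conclusion.** The concern holds. Under the plan's own rates and one-sided 0.05, the named test has 70.1% power at 274 and 72.6% at 288, not 80%. The risk of missing the assumed effect is about 30% at 274, where the plan implies 20%. Under the two-sided rule in Statistical methods, power is 57.7% to 60.7%.

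The Fisher figures are exact enumerations that rest only on the stated rates and equal arms. The alpha spending described in Sample size was not modelled; it would not raise power at the final analysis.

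**What to change.** Bring the test and the power into line before any comparison by arm is made. Either route keeps enrolment at 288.

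1. **Change the test (preferred).** Name the center-stratified Cochran–Mantel–Haenszel test without continuity correction for conversion. It matches the randomization, which the Allocation section stratifies by center. If an unstratified test is wanted, use mid-p or Boschloo. State the power for the chosen test at 288 and at 274 evaluable patients, with the center assumptions behind it.
2. **Keep Fisher's test and restate the power.** Give the power of 288 as about 73% at one-sided 0.05 or 61% at two-sided 0.05, whichever level the plan settles on.

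The cost is a few words in the protocol and one line of code. Under route 2 the stated power falls. Keeping both Fisher's test and 80% power would need 338 evaluable patients one-sided or 410 two-sided. A change of test made after unblinded results are seen would look driven by the data.
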